## 10 ADVERSE EVENTS

The Investigator is responsible for the detection and documentation of events meeting the criteria and definitions detailed below.

Participants will collect information about adverse events in their treatment diaries. However, they will be instructed to contact the clinical research team at any time after consenting to join the trial if they have an event that requires hospitalisation, or an event that results in persistent or significant disability or incapacity. The participants will be contacted weekly by a member of the research staff until they have reached their optimal dosage. Gabapentin is generally well tolerated in the management of other chronic pain conditions and SAEs are not anticipated. Any SAEs that occur after joining the trial will be reported in detail in the participant's medical notes and followed up until resolution of the event.

Full details of contraindications and side effects that have been reported following administration of the IMP can be found in the relevant Summary of Product Characteristics (SmPC).

Participants will be instructed to contact their Investigator at any time after consenting to join the trial if any symptoms develop. All adverse events (AE) that occur after joining the trial will be reported in detail in the Case Report Form (CRF) or AE form. In the case of an AE, the Investigator will ensure that the appropriate treatment is instigated by the appropriate medical personnel. Participants with AEs present at the last visit must be followed up until resolution of the event.

### 10.1 DEFINITIONS

An adverse event (AE) is any untoward medical occurrence in a clinical trial participant which does not necessarily have a causal relationship with an investigational medicinal product (IMP).

An adverse reaction (AR) is any untoward or unintended response to an IMP which is related to any dose administered to that participant.

An unexpected adverse reaction (UAR) is an adverse reaction that is not consistent with the applicable product information for the IMP, e.g. the SmPC for a licensed product.

A serious adverse event (SAE), serious adverse reaction (SAR) or suspected unexpected serious adverse reaction (SUSAR) is any AE, AR or UAR that at any dose:

- results in death;
- is life threatening\* (i.e. the participant was at risk of death at the time of the event; it does not refer to an event which hypothetically might have caused death if it were more severe);
- requires in-patient hospitalisation^ or prolongation of existing hospitalisation;
- results in persistent or significant disability or incapacity;
- is a congenital anomaly or birth defect.

^Any hospitalisation that was planned prior to randomisation will not meet SAE criteria. Any hospitalisation that is planned post randomisation will meet the SAE criteria.

### 10.2 DETECTING AEs AND SAEs

All AEs and SAEs will be recorded from the time a participant signs the consent form to take part in the study until end of treatment.

Participants will be asked to record the occurrence of AEs/SAEs in their treatment diaries during the study. They will not be asked to document the occurrence of any common ailments not associated with the drug eg colds and coughs. Open-ended and non-leading verbal questioning of the participant will be used to enquire about AE/SAE occurrence. Participants will also be asked if they have been admitted to hospital, had any accidents, used any new medicines or changed concomitant medication regimens. If there is any doubt as to whether a clinical observation is an AE, the event will be recorded. Participants will also be asked to record occurrence of any AEs in their daily treatment diaries. The participant's mood will be monitored by the research team using open ended questions during phone consultations and through the use of questionnaires at 3 and 6 months eg Hospital Anxiety and Depression Scale.

AEs and SAEs may also be identified by support departments e.g. laboratories.

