### 10.4 ASSESSMENT OF AEs AND SAEs

Seriousness, causality, severity and expectedness will be assessed as though the participant is taking active IMP. Cases that are considered serious and possibly related to IMP and unexpected (i.e. SUSARs) will be unblinded.

The Investigator is responsible for assessing each AE.

The Chief Investigator (CI) may not downgrade an event that has been assessed by an Investigator as an SAE or SUSAR, but can upgrade an AE to an SAE, SAR or SUSAR if appropriate.

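### The diary leaves out common ailments judged unrelated to the drug, although the protocol says all adverse events are recorded and the Investigator decides causality

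*Protocol*

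**What the plan says.** Four parts of the protocol bear on which events are captured.

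- **Definition (section 10.1).** An AE is "any untoward medical occurrence in a clinical trial participant which does not necessarily have a causal relationship with an investigational medicinal product (IMP"). Cause plays no part in it.
- **Scope (sections 10 and 10.2).** Section 10 states: "All adverse events (AE) that occur after joining the trial will be reported in detail in the Case Report Form (CRF) or AE form". Section 10.2 opens with the same scope, for the period up to when treatment finishes: "All AEs and SAEs will be recorded from the time a participant signs the consent form to take part in the study until end of" […].
- **Who judges (sections 10.4 and 10.4.2).** "The Investigator is responsible for assessing each AE". Section 10.4 has this done as though the woman were on active drug, and section 10.4.2 counts an event as related if a link is merely possible.
- **Diary (section 10.2).** After asking participants to note AEs and SAEs in the diary, the section adds: "They will not be asked to document the occurrence of any common ailments not associated with the drug eg colds and coughs". Later in the same paragraph it asks them to enter any AEs in the daily diary.

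Section 10 also carries two instructions on contacting staff. One tells women to contact the research team "if they have an event that requires hospitalisation, or an event that results in persistent or significant disability or incapacity". The other reads: "Participants will be instructed to contact their Investigator at any time after consenting to join the trial if any symptoms develop".

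**The concern.** A cold or a cough is an untoward medical occurrence, so under section 10.1 it is an AE and under sections 10 and 10.2 it is to be recorded. The diary sentence does not ask for it. The exclusion also depends on whether the ailment is associated with the drug, which is the question the protocol reserves for the Investigator.

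An event missing from the diary may never be assessed for relatedness or expectedness. How AEs are collected is fixed in this section of the protocol, so an analysis plan could not put it right afterwards.

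**Working it through.** No arithmetic applies. The protocol gives no AE rate and no figure that depends on this sentence. The check is to see whether the rules can be followed together, and then what the other safeguards catch.

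**Step 1: can the rules coexist?** Take a participant with a cold at week 10.

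| Rule | Is the cold captured? |
|---|---|
| 10.1, definition regardless of cause | It is an AE |
| 10 and 10.2, all AEs recorded | Yes |
| 10.2, later request to enter any AEs in the diary | Yes |
| 10.2, sentence on common ailments | Not asked for |

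The last row conflicts with the three above it, and two of the conflicting statements stand in the same paragraph of section 10.2.

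**Step 2: who applies the exclusion?** Sections 6.5 and 7.2 make the diary a daily record kept by the participant. No member of staff is present when an entry is made or left out. Colds and coughs are given as examples and not as a complete list, so someone must decide whether another ailment counts as common and as unrelated. In practice that is the participant.

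The boundary matters where symptoms overlap. Section 6.3 names somnolence and poor concentration among gabapentin's side effects. A woman who is drowsy and unfocused during a cold could put this down to the cold and enter nothing. Under section 10.4.2 the Investigator might have called the same symptoms possibly related.

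**Step 3: what do the other safeguards recover?**

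- *Open questioning by staff (10.2).* This can bring out events missing from the diary, but it needs a contact. Section 10 ends weekly contact when the optimal dose is reached, and section 7.2 makes the calls from week 2 conditional on unfinished escalation. The remaining planned visits are at week 6, 3 months and 6 months, so the last interval is 6 − 3 = 3 months and recovery depends on recall.
- *Specific prompts (10.2).* They cover hospital admission, accidents, new medicines and changed regimens. An untreated minor symptom triggers none of them.
- *Recording when in doubt (10.2).* This works only after staff have heard of the event.
- *Other diary items (7.2 and 8).* Concomitant medication, including non-prescription products, and healthcare visits leave a trace of an ailment that was treated or seen. Section 7.2 collects the diary at the 6-month visit.

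Recovery is therefore real but partial, and weakest for untreated minor events after titration.

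**Step 4: what depends on these events?** Section 2.2.1 sets two primary endpoints: the proportion of eligible patients randomised, and the proportion who take all medication and fully complete the final questionnaires. Neither uses AE entries. Section 9.2 (ii) assesses acceptability through focus groups, 6-month questionnaire items and self-reported compliance. Section 9 specifies no comparison of AE rates between arms.

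**The case against.** The sentence can be defended as a sensible limit on diary burden: it covers only common ailments, its examples are trivial, and it says women will not be asked for these entries, not that they must omit them. The diary's own wording is not shown and may give simple examples with no causality test. The safeguards in section 10.2 are real. All of this stands, and it limits the consequence to possible under-recording of minor events. It does not remove the contradiction, because a limit on diary burden can be set without reference to cause and without also stating that all AEs are recorded.

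Three stronger readings are tempting, and the protocol does not support them.

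- *AE counts are biased between arms because women who guess gabapentin will report more.* Section 5.5.2 describes packs of identical appearance, both arms receive the same instruction, and nothing in the protocol shows differential omission.
- *The omitted events are lost for good.* The questioning, prompts and doubt rule in section 10.2 can recover some of them.
- *The two contact instructions leave a life-threatening event without admission uncovered.* Both instructions go to participants and can be followed together. The one triggered by any symptoms includes the narrower one, so the overlap is redundant drafting and not a gap.

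**Conclusion.** The concern holds as an internal contradiction with a practical consequence. Section 10.2 conflicts with itself and with sections 10, 10.1 and 10.4, and its open-ended, cause-dependent exclusion hands the first causality judgement to the participant. Minor AEs may be under-recorded, chiefly untreated ones after weekly calls end.

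The number of events affected and any difference between arms cannot be derived from the protocol; any figure would be pure assumption. The primary feasibility endpoints are untouched. The conclusion rests on one reading: that the sentence governs the diary, as its position directly after the diary instruction indicates. The correction should still be made, because it changes which events reach the Investigator and costs little.

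**What to change.** Choose one of two courses.

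1. Delete the sentence on common ailments in section 10.2. Have the diary take any new or worsened symptom, and leave classification to the Investigator alone.
2. If the sponsor prefers to spare participants minor entries, name a closed list of ailments that are not recorded, whatever anyone thinks of their cause. Amend the statements about all AEs in sections 10 and 10.2 to match.

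Separately, and only as a tidy-up, reconcile the two overlapping contact instructions in section 10 into one.

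The cost is wording in section 10, the diary instructions and, where it repeats them, the participant information sheet. The first course also brings some more minor entries to code, a small burden in a trial of 60 women.

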### 10.3 RECORDING AEs AND SAEs

When an AE/SAE occurs, it is the responsibility of the Investigator to review all documentation (e.g. hospital notes, laboratory and diagnostic reports) related to the event. The Investigator will then record all relevant information in the CRF and on the SAE form (if the AE meets the criteria of serious).

Information to be collected includes dose, type of event, onset date, Investigator assessment of severity and causality, date of resolution as well as treatment required, investigations needed and outcome.

### 10.4 ASSESSMENT OF AEs AND SAEs

Seriousness, causality, severity and expectedness will be assessed as though the participant is taking active IMP. Cases that are considered serious and possibly related to IMP and unexpected (i.e. SUSARs) will be unblinded.

The Investigator is responsible for assessing each AE.

The Chief Investigator (CI) may not downgrade an event that has been assessed by an Investigator as an SAE or SUSAR, but can upgrade an AE to an SAE, SAR or SUSAR if appropriate.

#### 10.4.1 Assessment of Seriousness

The Investigator will make an assessment of seriousness as defined in Section 10.1.

#### 10.4.2 Assessment of Causality

The Investigator will make an assessment of whether the AE/SAE is likely to be related to the IMP according to the definitions below.

All AEs/SAEs judged as having a reasonable suspected causal relationship (ie possibly related) to the IMP will be considered as related to the IMP (ARs/SARs).

Where non Investigational Medicinal Products (NIMPs) e.g. rescue/escape drugs are given: if the AE is considered to be related to an interaction between the IMP and the NIMP, or where the AE might be linked to either the IMP or the NIMP but cannot be clearly attributed to either one of these, the event will be considered as an AR/SAR.

Unrelated: where an event is not considered to be related to the IMP.

Possibly Related: Possibly Related: The nature of the event, the underlying medical condition, concomitant medication or temporal relationship make it possible that the AE has a causal relationship to the study drug.

Alternative causes such as natural history of the underlying disease, other risk factors and the temporal relationship of the event to the treatment should be considered and investigated. The blind should not be broken for the purpose of making this assessment.

#### 10.4.3 Assessment of Severity

The Investigator will make an assessment of severity for each AE/SAE and record this on the CRF or AE form according to one of the following categories:

Mild: an event that is easily tolerated by the participant, causing minimal discomfort and not interfering with every day activities.

Moderate: an event that is sufficiently discomforting to interfere with normal everyday activities.

Severe: an event that prevents normal everyday activities.

Note: the term 'severe', used to describe the intensity, should not be confused with 'serious' which is a regulatory definition based on participant/event outcome or action criteria. For example, a headache may be severe but not serious, while a minor stroke is serious but may not be severe.

#### 10.4.4 Assessment of Expectedness

If an event is judged to be an AR/SAR, the evaluation of expectedness will be made based on knowledge of the reaction and the relevant product information documented in the SmPC.

The event may be classed as either:

Expected: the AR is consistent with the toxicity of the IMP listed in the SmPC.

Unexpected: the AR is not consistent with the toxicity in the SmPC.

### 10.5 REPORTING OF SAEs/SARs/SUSARs

Once the Investigator becomes aware that an SAE has occurred in a study participant, the information will be reported to the ACCORD Research Governance and QA Office immediately or within 24 hours. If the Investigator does not have all information regarding an SAE, they should not wait for this additional information before notifying ACCORD. The SAE report form can be updated when the additional information is received.

The SAE report will provide an assessment of causality and expectedness at the time of the initial report to ACCORD according to Sections 10.4.2, Assessment of Causality and 10.4.4, Assessment of Expectedness.

The SAE form will be transmitted by fax to ACCORD on [name] or may be transmitted by hand to the office.

All reports faxed to ACCORD and any follow up information will be retained by the Investigator in the Investigator Site File (ISF).

## **10.6 REGULATORY REPORTING REQUIREMENTS**

The ACCORD Research Governance & QA Office is responsible for pharmacovigilance reporting on behalf of the co-sponsors (Edinburgh University and NHS Lothian).

The ACCORD Research Governance & QA Office has a legal responsibility to notify the regulatory competent authority and relevant ethics committee (Research Ethics Committee (REC) that approved the trial). Fatal or life threatening SUSARs will be reported no later than 7 calendar days and all other SUSARs will be reported no later than 15 calendar days after ACCORD is first aware of the reaction.

ACCORD will inform Investigators at participating sites of all SUSARs and any other arising safety information.

A Development Safety Update Report (DSUR) will be submitted to the regulatory competent authority and main REC listing all SARs and SUSARs.

## **10.7 FOLLOW UP PROCEDURES**

After initially recording an AE or recording and reporting an SAE, the Investigator will follow each participant until resolution or death of the participant. Follow up information on an SAE will be reported to the ACCORD office.

AEs still present in participants at the last study visit will be monitored until resolution of the event or until no longer medically indicated.

## **11 PREGNANCY**

Pregnancy is not considered an AE or SAE; however, the Investigator will collect pregnancy information for any female participants who become pregnant while participating in the study. The Investigator will record the information on a Pregnancy Notification Form and submit this to the ACCORD office within 14 days of being made aware of the pregnancy.

All pregnant female participants will be followed up until following the outcome of the pregnancy.

Participants will be asked not to try and get pregnant for the duration of the study. Use of contraception will be recorded at screening.

## **12 TRIAL MANAGEMENT AND OVERSIGHT ARRANGEMENTS**

### **12.1 TRIAL MANAGEMENT GROUP**

The trial will be coordinated by a Project Management Group, consisting of the grant holders (Chief Investigator and Principal Investigator in Aberdeen), the Trial Manager and coordinating nurse.

The Trial Manager will oversee the study and will be accountable to the Chief Investigator. The Trial Manager will be responsible for checking the CRFs for completeness, plausibility and consistency. Any queries will be resolved by the Investigator or delegated member of the trial team.

A Delegation Log will be prepared for each site, detailing the responsibilities of each member of staff working on the trial.

### **12.2 TRIAL STEERING COMMITTEE**

A Trial Steering Committee (TSC) will be established to oversee the conduct and progress of the trial. The terms of reference of the Trial Steering Committee, the draft template for reporting and the names and contact details are detailed in Appendix 2. The TSC will meet before study starts and will meet at least once during the study. They will be sent updates on the progress of the study.

### **12.3 DATA MONITORING COMMITTEE**

An independent Data Monitoring Committee (DMC) will be established to oversee the safety of participants in the trial. The terms of reference of the Data Monitoring Committee and the names and contact details are detailed in Appendix 3. The DMC will meet before the study starts and will meet at least once during the study. They will be sent updates on progress of the study every 6 months.

### **12.4 INSPECTION OF RECORDS**

Investigators and institutions involved in the study will permit trial related monitoring and audits on behalf of the sponsor, REC review, and regulatory inspection(s). In the event of an audit or monitoring visit, the Investigator agrees to allow the representatives of the sponsor direct access to all study records and source documentation. In the event of regulatory inspection, the Investigator agrees to allow inspectors direct access to all study records and source documentation.

### **12.5 RISK ASSESSMENT**

An independent risk assessment will be performed by an ACCORD Clinical Trials Monitor to determine if monitoring is required and if so, at what level. An independent risk assessment will also be carried out by the ACCORD Quality Assurance Group to determine if an audit should be performed before/during/after the study and if so, at what locations and at what frequency.

### **12.6 STUDY MONITORING AND AUDIT**

An ACCORD Clinical Trials Monitor or an appointed monitor will visit the Investigator site prior to the start of the study and during the course of the study if required, in accordance with the monitoring plan. Investigator sites will be risk assessed by the ACCORD QA Manager, or designee, in order to determine if audit by the ACCORD QA group is required.

## 13 GOOD CLINICAL PRACTICE

### 13.1 ETHICAL CONDUCT

The study will be conducted in accordance with the principles of the International Conference on Harmonisation Tripartite Guideline for Good Clinical Practice (ICH GCP).

A favorable ethical opinion will be obtained from the appropriate REC and local R&D approval will be obtained prior to commencement of the study.

### 13.2 REGULATORY COMPLIANCE

The study will not commence until a Clinical Trial Authorisation (CTA) is obtained from the appropriate Regulatory Authority. The protocol and study conduct will comply with the Medicines for Human Use (Clinical Trials) Regulations 2004, and any relevant amendments.

### 13.3 INVESTIGATOR RESPONSIBILITIES

The Investigator is responsible for the overall conduct of the study at the site and compliance with the protocol and any protocol amendments. In accordance with the principles of ICH GCP, the following areas listed in this section are also the responsibility of the Investigator. Responsibilities may be delegated to an appropriate member of study site staff.

#### 13.3.1 Informed Consent

The Investigator is responsible for ensuring informed consent is obtained before any protocol specific procedures are carried out. The decision of a participant to participate in clinical research is voluntary and should be based on a clear understanding of what is involved.

Participants must receive adequate oral and written information – appropriate Participant Information and Informed Consent Forms will be provided. The oral explanation to the participant will be performed by the Investigator or qualified delegated person, and must cover all the elements specified in the Participant Information Sheet and Consent Form.

The participant must be given every opportunity to clarify any points they do not understand and, if necessary, ask for more information. The participant must be given sufficient time to consider the information provided. It should be emphasised that the participant may withdraw their consent to participate at any time without loss of benefits to which they otherwise would be entitled.

The participant will be informed and agree to their medical records being inspected by regulatory authorities and representatives of the sponsor(s) but understand that their name will not be disclosed outside the hospital.

The Investigator or delegated member of the trial team and the participant will sign and date the Informed Consent Form(s) to confirm that consent has been obtained. The participant will receive a copy of this document and a copy filed in the Investigator Site File (ISF) and participant's medical notes.

